**GWI Registry**

**“Opt Out” letter**

**Opted Out (refused)**

**Advertisements**

**Initial Screening**

**(Telephone)**

**INELIGIBLE**

**Medical Screening**

**INELIGIBLE**

**Eligible Volunteers**

**Treatment**

**Waitlist**

**Follow-up**

**Follow-up**

**`**

12. Sample Size Justification.

Our study is designed to give us adequate power to detect clinically meaningful differences between treatment groups. Previous acupuncture research using our main outcome, the SF-36, in pain conditions (41,52) show a consistent standard deviation of 20 points in the Physical Component Summary score of the SF-36 for both baseline values and change scores. Sixty individuals per group (total n=120) would offer us a power of 80% to detect the difference between groups of 7 points. Using Cohen’s d estimation of effect size (20):

[figure not shown]

A sample size of 60 will allow us to see a moderate effect. In further support of our main outcome a 7 unit improvement has been shown to be clinically relevant (97,55,78).

Although we do not expect attrition to be large, we expect a dropout rate of no more than 10% by the 8 week endpoint. This trial is longitudinal which could increase drop-out rate. Still a veteran’s population will be less mobile and may have fewer other options for care; both of these factors should increase adherence. We will thus oversample to a target sample size of 67 volunteers per group to assure that our power to detect effects is maintained. The resulting overall sample will be 134 (one treatment group and one wait list group).

13. Description of Informed Consent Process.

The informed consent process will occur in two stages. Verbal informed consent will be administered prior to the initial telephone screening, and written informed consent will be administered in person, at the start of the screening visit.

A. Verbal Informed Consent for Telephone Screening: The first section of the Telephone Screening instrument is a script for informed consent. The Research Assistant will identify him/herself and the name of the study, determine if this is a good time for the volunteer to talk, and then give an explanation of the nature and purpose of the study. This will be similar to that provided in the written Informed Consent document but will be formatted as a series of bullet points to facilitate verbal communication between the Research Assistant and the volunteer. The volunteer will be asked if he/she has any questions. Any questions which the Research Assistant does not feel capable to answer, or for which the volunteer would like additional information, will be referred to the Study Coordinator, Principle Investigator, or Medical Advisor, as appropriate.

Next, the Research Assistant will ask the volunteer’s permission to ask him/her a series of questions to gauge eligibility for the study. The volunteer will be given an estimated time for the interview and told that some of the questions are about symptoms that he/she might experience; that some people might find some of the questions to be personal or distressing; that they can stop the interview at any time, should they choose not to continue; and that neither eligibility, participation, or non-participation in the study will in any way affect their benefits or any care that they may be receiving from the VA or elsewhere. The volunteer will be asked if they wish to continue with the screening interview, and if they say “yes”, a box indicating such will be checked on the screening form, and the date and interviewer’s initials filled in next to it. If the volunteer says “no”, they will be thanked for their time and willingness to hear about the study, the interview will be terminated, and the “No” box will be checked, dated, and initialed. At the end of the screening interview, eligible volunteers will be scheduled for an in-person screening visit at the Veteran’s Administration Hospital, Boston MA. 2 copies of the approved study consent form will be mailed to the volunteer when the appointment is scheduled. The volunteer will be encouraged to share this information with family members and medical care providers/counselors, and will be given a number to call if he/she has any additional questions prior to the screening visit.

B. Written Informed Consent process: At the beginning of the in-person screening visit, the Research Assistant will review each point of the Informed Consent document with the volunteer, in a private area. The Research Assistant will explain to the volunteer that it is possible that they may not be eligible for the study based on the results of the screening visit; however, if they are found to be ineligible, or change their mind about being in the study, they can be referred to acupuncturists in the community where they may be able to seek treatment on their own, should they wish. The volunteer will be encouraged to ask questions. If/when the staff member is assured that the volunteer understands the information in the Consent document, and is willing to proceed with secondary screening and potential enrollment in the study, the volunteer will be asked to sign 2 copies of the consent document, which will be co-signed and dated by the Research Assistant. One copy will be given to the volunteer, and the other will go into the volunteer’s chart. Should the volunteer be enrolled in the study, this document will be kept in a separate locked file from study data, along with other records containing the volunteers’ name or contact information.

Since this study is limited to United States veterans with Gulf War Syndrome, we do not expect volunteers to be minors, illiterate, or unable to speak or understand English.

14. Volunteer Screening Procedures.

Following the informed consent process volunteers will be given the check list of symptoms used to determine eligibility to the Gulf War Registry as described in “item 10 Inclusion/Exclusion”. Each volunteer will be screened by the study physician for general physical health status, physical and mental factors as described in the “Inclusion/Exclusion”, and asked to complete the Primary Care Evaluation of Mental Disorder (81).

15. Study Procedures/Study Interventions

Acupuncture intervention:

Participants will be given appointments to visit study acupuncturists for initial evaluation and treatment. During the first session, the acupuncturist will conduct an interview reviewing the volunteer’s medical history and presenting symptoms. During the physical examination, the practitioner evaluates areas of pain and aspects of diagnosis from the perspective of Traditional Chinese Medicine (TCM), including condition of the tongue, pulse, channels, and acupoints. The volunteer’s most distressing and other significant symptoms are identified and evaluated for TCM diagnosis. Each volunteer will receive an individualized treatment protocol that specifically addresses his or her unique pattern of symptoms. Individualized treatment is especially well suited for the highly variable presentation of Gulf War Illness (GWI), and pragmatic design acupuncture treatment trials have shown effectiveness for pain (91). Our study investigators have previously and with success used a technique of diagnosis and treatment called manualization (75); this technique shapes providers’ choices when best practice evidence is available allowing for improved replicability of treatments. Although symptoms of GWI have been successfully treated with acupuncture, a manualized approach would be premature. Thus we are allowing for fully individualized treatments and using accepted TCM data collection tools (included in “Section B. Surveys, Questionnaires, and Other Data Collection Instruments”) to record each treatment in detail.

Participants will receive acupuncture in private exam rooms in sessions that last about an hour. Brief interviews begin each subsequent session to review progress, prioritize symptoms, and identify any questions or concerns. After needle insertion, volunteers can expect to rest comfortably or nap. From 10 to 35 sterile, disposable needles will be inserted, with a technique characteristic of TCM known as “obtaining *de qi*,” an elicited response felt by both the patient and the acupuncturist. The needling sensation, adjusted for the comfort and safety of each patient, may be experienced as a pinch that rapidly subsides, or a sense of spreading pressure, dull ache, or warmth. Several types of needles, including from 32 to 38 gauge, and lengths from 15 mm to 50 mm, will be used on various parts of the body. Insertion depths vary by location, from subcutaneous to about 25 mm. Needles are retained 30-45 minutes. Choice of acupoints may vary during subsequent treatments to improve results.

A number of co-interventions will be used to supplement manual needling, usually 1 or 2 in each session, at the discretion of the acupuncturist. Electroacupuncture will be used for its efficacy in reducing pain and inflammation (59). Heat therapies will be used when appropriate, including heat lamp and moxibustion, a process in which a topical herbal product is heated on the needle or skin. Tui na, cupping and gua sha will be used, massage techniques in which rubbing, pressing, and scraping are applied to the body with the hands or with instruments. To prolong effects of treatment, tiny metallic balls, tacks or magnets may be applied to points after needling. The initial dose of acupuncture will be twice per week for 2 months, after which outcomes will be assessed and biological samples collected. For the following 4 months of treatment, the dose is reduced to once per week. The tapered dose of acupuncture is frequently used in clinical practice and has previously been used in research that demonstrated acupuncture efficacy for pain (9).

Volunteers in the control group will be offered 4 months of acupuncture once per week after the 2-month waiting period has elapsed. All volunteers will complete re-evaluation of outcomes instruments and biomarkers at the 6-month follow-up.

Patient charts will include complete details of each volunteer’s assessment, diagnosis, and treatment. Interview guides in use at the New England School of Acupuncture’s clinic will be used in this study: Health History Questionnaire, TCM Intake, and TCM Follow-up (included in “Section B. Surveys, Questionnaires, and Other Data Collection Instruments”). As part of standard clinical practice, the acupuncturists’ notes will include assessment of response to treatment and any adverse events. Patients’ medical records will be stored in locked offices or filing cabinets, in compliance with regulations of privacy and security mandated by the Health Insurance Portability Act of 1996 (HIPAA).

Numerous studies have shown that acupuncture is safe when provided by professionally trained practitioners. Minor adverse effects of acupuncture may include needling pain, hematoma, and slight bleeding at the needle sites, as well as transient dizziness or drowsiness. (54). Serious adverse events are extremely rare**.** In a systematic review of 12 prospective studies scrutinizing over a million treatments, the very low risk of serious adverse event, mostly trauma from needle puncture or infection, was estimated at 0.05 per 10,000 treatments, a risk below that of many common medical treatments (95).

Several hypotheses of the mechanisms of acupuncture explain its likely effects on the symptoms of GWI. Acupuncture’s effects on peripheral nerves as well as the central and autonomic nervous systems play a role in its analgesic and anti-inflammatory effects. Although the etiology of GWI is unknown, researchers suspect that the symptoms reflect a spectrum of neurologic injury (16,86). Regulation of the endocrine system, mediated by the hypothalamus-pituitary-adrenal (HPA) axis (59), suggests a likely role for acupuncture in reducing stress. While GWI is not defined as a psychiatric disorder like posttraumatic stress disorder (PTSD), stress does play a role in the etiology of other multisymptom illnesses, such as irritable bowel syndrome, multiple chemical sensitivity and chronic headache (10). Stress reduction is likely to be of significant benefit, not only to those volunteers with emotional and cognitive disturbances, but to all the volunteers.

16. Description of Protocol Drugs or Devices.

No drugs are used in this study. The devices used are described in section “15. Study Procedures/Study Interventions” above.

17. Laboratory Evaluations.

We will be collecting a small blood sample at the three data collection points and a research assistants will immediately transport the blood on ice to [name] lab. We are collecting and analyzing these data to better understand the mechanisms of GWI and changes associated with acupuncture. We are focusing on inflammatory changes, immune function, and markers of stress. For example we are interested in the relationship between acupuncture treatment, reported stress, and immune function. Multiple studies have looked at this relationship. For example recent research suggests that acupuncture modulates serum concentrations of inflammatory cytokines; for example, acupuncture reduces cytokine levels in a rat model of inflammation (79) and in asthmatic patients receiving a gentle form of Korean acupuncture (42). It is not surprising then that we have found in our IBS data set that individuals with greater decreases in reported stress had associated immunological changes as measured by a reduction in the percentage of circulating activated T-lymphocytes (CD69+). Toward the exploration of immunophenotyping, blood will continue to be collected with patient consent at the initial screen, at midpoint and at follow up. Mononuclear cells will be stained with a panel of antibodies (DAKO Cytomation) against markers of leukocyte differentiation and activation and analyzed using the Cell Quest program as described above. In parallel, serum cytokine levels (IFNγ, IL-2, IL-2R, IL-7, IL-4) will be measured by ELISA (R&D systems) and serum cortisol levels, as a surrogate biological marker for stress, by a radioimmunoassay. The evaluations at 3 different time points will enable us to identify immunological markers that are predictive of clinical response to acupuncture treatment (initial point) or are associated with it (endpoint). Initial analysis will be performed using ANOVA factorial with Bonferroni correction for multiple comparisons and ANOVA repeated measures for the overtime changes in immune status. If the results of this analysis warrant, a feature selection multivariate analysis will be performed that takes into account higher order interactions among the variables.

18. Data Analysis.

For our calculations, we will use the normal distribution assumption and explore this using a normal plot and goodness of fit test. If violations are found, non-parametric tests or transformations will be utilized. Variance equivalence will be tested using the F-test. Our protocol is designed to assure sample independence and adherence will be closely monitored. Before beginning the main statistical analyses, baseline variable levels across groups will first be considered to assess group equivalence. If the groups are not balanced on any baseline characteristics, these factors will be considered as variables in later multi-variate regressions.

The Centers for Disease Control defines Gulf War Illness (GWI) or Complex Multisymtom Illness (CMI) as the presence for at least 6 months of one or more self-reported symptoms from at least two clusters of symptoms: Cluster A (fatigability), Cluster B (Mood and Cognition), Cluster C (Musculoskeletal) (10). A single measure of severity that addresses all possible presentations of GWI does not exist. Thus we chose to use as the main outcome a general measure of health. Our primary outcome, the SF-36 (53) is a 36-item measure of global health. It is well recognized with good reliability and validity. Items address multiple aspects of physical and mental health as well as functionality. Eexperience to date from nearly 400 randomized controlled clinical trials suggests that the SF-36 is also a useful tool for evaluating the benefits of alternative treatments (88).

Comparisons between the treatment and wait-list groups will be based on improvement in SF-36 scores. We are considering the primary outcome to be the Physical Component Summary score of the SF-36. We chose to use the SF-36 in order to show general health related quality of life in this population with very diverse complaints. The Physical component subscale was chosen because it focuses on 2 of the three Centers for Disease Control GWI clusters (fatigue and musculosketal complaints). Statistically we will test mean differences between groups following 2 months of treatment using Student’s t-tests at an alpha=0.05. Analyses of secondary outcomes will include a test for mean differences between groups using student’s t-tests at an alpha=0.05.

As GWI is a complex disease with multiple symptom manifestations, we have included measures of global change as well as changes in specific symptoms of interest. These include areas suggested in the Program Announcement as well as one tailored measure described in Appendix 8) that allows volunteers to identify and report changes in their most important symptoms. Our secondary analyses will include a within-groups comparison within CDC clusters for changes baseline to endpoint (2 months of treatment). Cluster A, fatigability, will be assessed using by the Multidimensional Assessment of Fatigue (85). Cluster B, mood and cognition, will be assessed using The Profile of Mood States (62). Cluster C, musculoskeletal complaints, will be assessed using the McGill Pain Scale (55). All of these scales are well recognized in the scientific literature and have shown good reliability and validity.

Our measurements include:

Screening:

- Primary Care Evaluation of Mental Disorder (Prime MD) (81)

Data Collection:

- - The Sf-36 (53)
- Multidimensional Assessment of Fatigue (85)
- The Profile of Mood States (62)
- Pittsburg Sleep Quality Index (34)
- Measure Your Medical Outcomes Profile (40)
- Beck Anxiety Inventory (63)
- McGill Pain Scale (55)
- Carroll Depression Scale (14)
- Social support, Social Networks, and Stress (56-7)
- Medication use and Expectations for Treatment
- Blood draw to examine levels of selected markers of inflammation, stress, and immune function.

The PRIME-MD will be used as part of our medical screening procedure. It was developed by [name] and colleagues to assist general practitioners in the diagnosis of minor psychiatric disorders. The questionnaire consists of two parts, a self-report patient questionnaire, and a series of interview models for mood disorder, anxiety disorder, psychosomatic disorder, alcohol abuse and eating disorder. It shows good reliability and validity (70,81)

The SF-36 is a multi-purpose, 36 item health survey. It yields an 8-scale profile of functional health and well-being scores as well as psychometrically-based physical and mental health summary measures and a preference-based health utility index. It is a generic measure, as opposed to one that targets a specific age, disease, or treatment group. Accordingly, the SF-36 has proven useful in surveys of general and specific populations, comparing the relative burden of diseases, and in differentiating the health benefits produced by a wide range of different treatments (53).

The 16 item Multidimensional Assessment of Fatigue (MAF) scale measures four dimensions of fatigue: severity (#1-2), distress (#3), degree of interference in activities of daily living (#4-14), and timing (#15-16). Fourteen items contain numerical rating scales (#1-14) and two items have multiple-choice responses (#15-16). Respondents are asked to reflect over the past week. The MAF is a revision of the Piper Fatigue Scale, a 41-item measure of fatigue developed for research purposes and tested with oncology patients (68,85).

The Profile of Mood States (POMS) assessment has been used since1971 to measure of mood states and their fluctuations in ill and healthy populations. The POMS Standard assessment is a factor-analytically derived inventory that measures six identifiable mood or affective states. It shows good reliability, validity, and usability (61)

The Pittsburg Sleep Quality Index is a well-used and validated scale that measures various qualities of the subject’s sleep. It has shown good reliability (34).

The Measure Your Medical Outcomes Profile is a three item measure that allows participants to name their main complaints and rate the severity of them over time (40l).

The Beck Anxiety Inventory (BAI) measures the severity of anxiety in adults and adolescents. This 21 item measure can be self-administered and evaluates both physiological and cognitive symptoms of anxiety and item overlap with other self report depression inventories is minimized. Each item is descriptive of a symptom of anxiety and is rated on a scale of 0 to 3. It shows good reliability and validity (63).

The McGill Pain scale is perhaps the most recognized and utilized pain measurement device across a range of ailments. This 15 item measure asks participants to describe the quality of their pain using various different descriptors (55).

The Social Support, Social Networks, and stress measures address the quality and quantity of the volunteer’s social world. These measures have been found to correlate and predict various in stress and other health outcomes (56-7).

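### The claimed 80% power for a 7-point PCS difference with 60 per group is about 48% on the protocol's own SD of 20

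*Protocol*

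**What the plan says.** Protocol section 12 (Sample Size Justification) cites earlier acupuncture studies in pain conditions which, it says, "show a consistent standard deviation of 20 points in the Physical Component Summary score of the SF-36 for both baseline values and change scores". It then states: "Sixty individuals per group (total n=120) would offer us a power of 80% to detect the difference between groups of 7 points". A Cohen's d formula follows, as a figure that is not reproduced in the text, and then: "A sample size of 60 will allow us to see a moderate effect". The choice of difference is supported by the statement that "a 7 unit improvement has been shown to be clinically relevant".

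For attrition the section says "we expect a dropout rate of no more than 10% by the 8 week endpoint", and concludes: "We will thus oversample to a target sample size of 67 volunteers per group".

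Section 18 (Data Analysis) fixes the endpoint and the test: "We are considering the primary outcome to be the Physical Component Summary score of the SF-36", and "Statistically we will test mean differences between groups following 2 months of treatment using Student’s t-tests at an alpha=0.05". It does not say whether the test is one- or two-sided. It names no covariate-adjusted primary analysis, and no other SD for the PCS appears in the protocol.

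**The concern.** Everything needed to recompute the power is in the text: SD, difference, group size, alpha and test. A difference of 7 on an SD of 20 is 0.35 SD. Sixty per group is roughly what a two-group t-test needs for 0.5 SD, so the 80% looked too high.

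Section 12 opens by promising adequate power for clinically meaningful differences, names 7 points as such a difference, and oversamples in order to preserve the power. If the true figure is near 50%, that promise is not met. A non-significant primary result, read against a claimed 80%, would be taken as fairly good evidence against a 7-point benefit when it would often be compatible with one.

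**Working it through.** **Inputs**

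| Quantity | Value | Source |
|---|---|---|
| SD of PCS, baseline and change | 20 | Section 12 |
| Difference to detect | 7 points | Section 12 |
| Analysed per group | 60 | Section 12 |
| Randomised per group, 10% dropout | 67 | Section 12 |
| Test | Student's t, between groups, alpha 0.05 | Section 18 |
| Sides | two (assumed; one-sided also tried) | not stated |

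**Step 1: dropout inflation.** 60/0.9 = 66.7, so 67 per group. This figure reproduces.

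**Step 2: the stated power.**

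- Standardised difference: d = 7/20 = 0.35.
- Standard error of the difference: 20 × √(2/60) = 3.65.
- Expected test statistic: 7/3.65 = 1.92, which is below the two-sided critical value of 1.96.
- Normal approximation: power = Φ(1.917 − 1.960) = Φ(−0.043) = 48.3%.
- Noncentral t with 118 degrees of freedom: 47.7%.

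The stated 80% does not reproduce. Because the protocol gives SD 20 for change scores as well, testing change from baseline instead of the 2-month value gives the same result.

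**Step 3: other readings of the plan (difference 7, SD 20).**

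| Reading | Power |
|---|---|
| 60 per group, two-sided 0.05 | 48% |
| 60 per group, one-sided 0.05 | 60% |
| 60 per group, one-sided 0.10 | 74% |
| 67 per group (no dropout), two-sided 0.05 | 52% |
| 54 per group, two-sided 0.05 | 44% |
| One-sample test, n = 60, two-sided 0.05 | 76% |

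The 54 is a scenario: section 11 gives a recruitment target of 120, and 60 × 0.9 = 54 would remain if only 120 were enrolled and 10% dropped out. The one-sample test is not the planned analysis.

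**Step 4: what would give 80% (two-sided 0.05).**

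- *Group size:* n = 2 × (1.960 + 0.842)² × 20²/7² = 2 × 7.85 × 400/49 ≈ 128.1, so 129 per group by the normal approximation and 130 by noncentral t. With 10% dropout, 129/0.9 to 130/0.9 is 144 to 145 per group, or 288 to 290 in total.
- *Difference, with 60 per group and SD 20:* 10.3 points by noncentral t (d = 10.3/20 = 0.52). The normal approximation gives 2.80 × 3.65 = 10.2.
- *SD, with 60 per group and 7 points:* at most about 13.6. Power for 7 points is 72% at SD 15, 89% at SD 12 and 97% at SD 10.

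**Step 5: precision.** The half-width of the 95% confidence interval is 1.980 × 3.65 = 7.2 points with 60 per group, so an observed difference of exactly 7 would narrowly miss significance. With 67 per group analysed it is 1.978 × 3.46 = 6.8 points, and an observed 7 would just reach it.

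**Step 6: baseline adjustment (not the planned primary analysis).** If baseline and follow-up have the same SD, the variance of change is 2 × 20² × (1 − ρ). Setting this equal to 20² gives ρ = 0.5. The adjusted SD is then 20 × √(1 − 0.25) = 17.3, which gives 59% power for 7 points and 80% power for 8.9 points. Power for 7 points is 51% at ρ = 0.3 and 76% at ρ = 0.7.

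**The case against.** The strongest reply concerns the SD. The value of 20 comes from cited studies that cannot be checked here. If the PCS in this trial has a much smaller SD, the actual power could be close to 80% or above it. That is true, and it is why the 48% is conditional on SD 20. It does not rescue section 12, because either the power or the SD printed there must then be wrong.

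A second reply is that the sentence about a moderate effect is roughly right taken alone: at d = 0.5, 60 per group gives 78% power. This stands. The fault lies in placing 7 points beside it, since d = 0.5 is 10 points at SD 20. The formula that is not shown may explain what was meant by moderate, but it cannot change 7/20, because both numbers are in the text.

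Third, the trial might still exclude a 7-point benefit, depending on the estimate and SD observed. This also stands: low power makes an inconclusive result likely, not certain.

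Finally, the side of the test is not stated. A one-sided 0.05 test gives 60%, still 20 percentage points short.

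**Conclusion.** The stated power is wrong on the protocol's own inputs. With SD 20, 60 analysed per group and a two-sided t-test at 0.05, power for 7 points is 48%, not 80%: a shortfall of 32 percentage points, and a 52% chance of missing a true 7-point benefit. None of the alternative readings tried reaches 80%. The internal contradiction is certain. The 48% itself rests on SD 20 and on a two-sided test. How the error arose cannot be told from the document. Because the recruitment target and the oversampling both rest on this figure, it must be corrected.

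**What to change.** Keep the sample size and restate section 12, for example: *With 60 analysed per group, SD 20 and two-sided alpha 0.05, the trial has 80% power for a difference of 10.3 points (d = 0.52) and 48% power for 7 points; the expected 95% confidence interval half-width is 7.2 points.*

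In the same edit:

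- Say that the test is two-sided.
- Tie the moderate-effect sentence to about 10 points, not to 7.
- Amend the opening claim of adequate power for clinically meaningful differences, and the statement that oversampling maintains power, so that neither contradicts the new figures.
- Confirm that 20 is the SD of the PCS as it will be scored. If it is not, replace it and recompute.

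If a baseline-adjusted primary analysis is adopted, quote its figures instead, with the assumed correlation: at 0.5, 80% power for about 8.9 points and 59% for 7 points.

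The cost is protocol wording and a less favourable stated power, with no extra patients. Keeping the 80% claim for 7 points at SD 20 under the planned t-test would instead mean enrolling about 144 to 145 per group.
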